### 2.2. Study objectives and endpoints

#### 2.2.1. Main objective and endpoint

The main objective of the study is to evaluate the plasma levels of hPG_80_ (circulating progastrin) during therapeutic follow-up and relapse monitoring among patients with high-grade glial tumors.

The primary endpoint is hPG_80_ plasma concentrations measured by BIODENA CARE using their DxPG80 IVD ELISA kit, from inclusion to the last follow-up.

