#### 2.2.2. Secondary objectives

The secondary objectives are:

– To study hPG_80_ concentrations according to tumor progression using the Response Assessment in Neuro-Oncology (RANO) criteria, which take progression objectified by imagery, clinical status and level of steroid therapy into account.– To evaluate the sensitivity to irradiation of hPG_80_ concentration variations.– To compare hPG_80_ plasma levels in patients, and to study inter-individual variations before, after and during disease management.

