### 2.4. Intervention

Eligible patients will be included during a consultation with an investigator after verification of their compliance with the inclusion and non-inclusion criteria (and signing of informed consent).

A fasting blood sample will be taken on the start and end day of radiotherapy and during adjuvant chemotherapy (every 3 cycles). Follow-up monitoring will be performed for 9 months, with a blood sample taken every 3 months on the day of the follow-up MRI.

Pseudonymized blood samples will be stored at the Centre Jean PERRIN and then sent to the Hospices Civils de Lyon (France) for analysis. The blood samples will be analyzed to evaluate the plasma concentrations of hPG_80_ in pmol/L using the ELISA DxPG80 kit (BIODENA CARE, France).

The risks or constraints appear minimal for the subjects participating in the study since the only interventions are blood tests.

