**Tumor evaluation**							
MRI (rano evaluation)		✓	✓^*^	✓	✓	✓	✓

* Optional: If performed in standard practice.

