### 2.8. Data analysis

The main analysis consists of the descriptive analysis of plasma prograstin concentration values at each time point. For the third secondary objective, this analysis will be further developed by taking into account the longitudinal character of the data and by modeling data using mixed effects regression models, associated with graphical representations of individual trajectories.

The study of the relationship between hPG_80_ concentrations and tumor evaluation according to the RANO criteria (secondary objective 1) at different time points will be performed using generalized linear mixed models with response as the dependent variable, with hPG_80_ concentration as a fixed effect (as well as possibly other covariates), and with random effect calculations enabling the modeling of repeated data during follow-up.

The impact of radiotherapy on the variations in hPG_80_ concentrations (secondary objective 2) will be investigated using linear mixed models, followed, if relevant, by a *post-hoc* analysis by paired sample comparison tests.

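### For a lasting progression outcome, the objective-1 model (RANO response as dependent variable) is confounded by time without a time term and not estimable with one

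*Protocol article*

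**What the plan says.** The first secondary objective (section 2.2.2) is "To study hPG_80_ concentrations according to tumor progression using the Response Assessment in Neuro-Oncology (RANO) criteria". Here hPG80 is the quantity compared and progression defines the groups.

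Section 2.8 analyses this objective "using generalized linear mixed models with response as the dependent variable". hPG80 enters "as a fixed effect (as well as possibly other covariates", and the repeated visits are handled "with random effect calculations enabling the modeling of repeated data during follow-up". No time term is named.

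Table 2 schedules RANO evaluation at the first and last radiotherapy sessions (the latter "Optional: If performed in standard practice"), every three adjuvant cycles, and at 3, 6 and 9 months. hPG80 is measured at the same visits. The primary endpoint runs "from inclusion to the last follow-up" (section 2.2.1). The article does not say whether response is binary or has several levels, whether progressed status is carried forward, or whether visits after progression are used.

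**The concern.** The objective asks how hPG80 differs by progression status, but the model predicts status from hPG80. That matters because of how progression behaves. If it is scored yes/no and persists, each patient's series is a run of zeros followed by a run of ones, and the proportion progressed can only rise over visits. Time is then strongly related to the outcome.

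The article also gives reason to expect hPG80 to change over time. The Introduction reports raised GAST expression after irradiation and a fall in the marker after total resection, and objective 2 is about its change with irradiation. The analyst must therefore either leave time out and risk confounding, or put it in and face a run-of-ones outcome that a patient random intercept plus time can fit almost perfectly.

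At stake is the only planned analysis that links the marker to progression, and the Discussion looks ahead to a larger study.

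**Working it through.** **The plan's own figure.** The article gives no figure for objective 1. Its one design figure (30 patients, 80% power, effect size 0.75, two-sided 5%) concerns patients against healthy subjects. It reproduces as a 1:1 two-group comparison: n = 2 × (1.960 + 0.842)² / 0.75² ≈ 28 per group, and the two-sample t-test power with 30 per group is 81.5%. It has no bearing on this point.

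**Model examined.** For patient i at visit j, with y = 1 if progressed:

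logit P(y_ij = 1) = α + β·hPG80_ij [+ γ·time_j] + b_i, with b_i ~ N(0, σ²).

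From the article: 30 patients, hPG80 as fixed effect, a random effect for repeated data, and other covariates possible. Assumed: binary coding, a random intercept, 5 to 7 visits, and the progression rates and hPG80 variation given below.

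**Why progression follows time.** Assume an 18% hazard per visit from the third visit. The cumulative proportion progressed at visit k is 1 − 0.82^(k−2): 18%, 33%, 45%, 55% and 63% at visits 3 to 7. With 30 patients that is 30 × 0.63 ≈ 19 progressions by visit 7. A 10% drift per visit multiplies hPG80 by 1.10⁵ ≈ 1.6 between visits 1 and 6. Two quantities that both trend over visits will correlate without any link between them.

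**Case 1: status persists, later visits kept, no time term.** This is the model with only the terms that section 2.8 names. Estimates are finite. With log SDs of 0.85 between and 0.5 within patients, the median σ over repeated runs was 1.58 to 1.65 with no true link and 2.61 to 3.13 with a true doubling at progression. It reached its bound in 0% of fits. The weakness is confounding. Results with 6 visits and 200 trials per row (likelihood-ratio test):

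| Assumed hPG80 drift per visit | True link | Rejections | Median OR per doubling |
|---|---|---|---|
| none | none | 6.5% | – |
| about 10%, up or down | none | 50–51% | 1.56 or 0.64 |
| about 20%, up or down | none | 97–98% | 2.7 or 0.36 |
| about 20%, down | 1.5-fold rise | – | 0.85 (wrong direction) |

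A separate refit at 10% drift gave about 53% false positives.

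**Case 2: status persists, later visits kept, time term added.** Let α, β, γ and σ all grow by a common factor. Each fitted curve tends to a step at a patient-specific time, which is the shape of a zeros-then-ones series. The likelihood has no finite maximum in σ, and β grows with it.

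- σ was at its upper bound in 70–100% of fits in the refit. The median OR per doubling was 9.5 with a bound of 7.4 and 125 with a bound of 20. Two other runs of the same scenario gave about 10 and 152, and 9.6 and 163.
- In a different set-up (5 visits, generating log-OR 0.7 per SD of hPG80, within-patient correlation 0.2 or 0.8), σ was at its bound in 97–100% of fits. The median log-OR rose from 1.2 to 4.4 (correlation 0.2) and from 2.6 to 7.6 (correlation 0.8) when the bound went from 10 to 40.

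**Case 3: visits dropped after first progression.** Without time, σ collapsed to about zero in 90–100% of fits and the log-OR was stable at about 0.6 for a generating 0.7, so the random effect does nothing. With time, σ exceeded 10 in 15–95% of fits.

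**Case 4: status can revert (15% or 30% per visit).** Median σ was 1.5 to 2.8 and the median log-OR 0.46 to 0.89, with or without time, and never at the bound. In the other set-up with 30% reversion, σ was at its bound in at most 2.5% of fits, and the OR did not depend on the bound.

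**The alternative.** A linear mixed model with log hPG80 as outcome, under the same assumed SDs, returned a ratio of 1.98 for a true 2.0. It had 5.2% false positives in 2,000 null trials and 92% power for a ratio of 1.5. Visit as a fixed effect absorbs a drift common to all patients.

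**The case against.** A reader might infer that the model as written must fail to converge because progression is entered only once. The documents do not support that. Section 2.8 names no time term, and without one the same zeros-then-ones series give finite, stable estimates. Divergence needs three things together: binary coding, persisting status with later visits kept, and a time covariate. The article states none of them. RANO is evaluated at each MRI and takes imaging, clinical status and steroids into account, so a visit-level category could change between visits, and a generalized model could be ordinal. All of this stands and limits the point.

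It can also be said that marker as predictor and response as outcome is a legitimate direction, and that section 2.8 describes the aim as a relationship, which is symmetric. That stands too: the direction alone is a mismatch with section 2.2.2, not an error. Nor is it a finding that coding, post-progression visits and covariates are left open, since an article commonly leaves these to the full protocol or analysis plan.

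What the objection does not remove is that section 2.8 does fix the dependent variable. For the progression outcome that section 2.2.2 names, if status persists, leaving time out only exchanges non-estimability for confounding.

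**Conclusion.** The point holds conditionally. If the objective-1 outcome is progression yes/no and a progressed patient stays progressed, the stated model has no good form while later visits are kept. Without time, an assumed 10% drift in hPG80 per visit yields about 50% false positives. With time, which the wording on other covariates allows, the odds ratio is set by the software's bound (9.5 against 125 in one comparison).

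These sizes rest on the assumed hazard, hPG80 variation and drift. The size and direction of any real drift are unknown; with none, the false-positive rate was 6.5%. The point does not extend to the model without time as a convergence failure, or to a RANO status that can revert, where the fit is stable with time included.

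The change is worth making but not critical: this is a secondary objective of a 30-patient pilot, and the descriptive main analysis is untouched.

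**What to change.** For objective 1, replace the response model with a linear mixed model:

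log hPG80_ij = visit_j + δ·(progressed at visit j) + b_i + e_ij,

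with RANO progression status at that visit as a time-varying fixed effect, visit as a fixed effect and patient as a random effect. Report exp(δ), the hPG80 ratio for progressed versus not progressed, with its 95% CI. This matches section 2.2.2 and uses the class of model already planned for objective 2.

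If progression itself is to be modelled, use a discrete-time hazard model to first progression, with visit terms, hPG80 as a time-varying covariate and no patient random effect.

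The cost is one paragraph of analysis wording. The main result becomes a fold difference in hPG80 rather than an odds ratio for response, and the optional hazard model discards visits after progression. The log scale also needs a rule for undetectable values: the Introduction reports detection in 69% of glioblastoma patients after surgery, so about 100 − 69 = 31% were undetected. The 92% power figure comes from simulated log-scale values without such a feature among its stated assumptions, so it may be optimistic.

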### 2.9. Data management and monitoring

The data collected for the study will be recorded on an eCRF (Ennov Clinical software). The users with access to the data will be the investigators, the clinical research associates, the project leaders and the biostatisticians. They are authorized professionals and are subject to professional secrecy. The investigator will ensure the accuracy, completeness, and consistency of the data recorded (pseudonymized patient data) and of the provision of answers to data queries.

A clinical research associate mandated by the sponsor will perform regular monitoring reviews. The objectives will be to ensure the proper conduct of the study, the recording of the data generated in writing, and its documentation, storage and reporting, in accordance with the legislative and regulatory provisions in force. The follow-up reports will ensure traceability.

### 2.10. Consideration of risk of bias

The risk of selection bias should be limited by an exhaustive inclusion of eligible patients treated at the Centre Jean PERRIN during the study period. As recruitment is consecutive, a list of potentially eligible patients will be kept, in order to verify a posteriori the representativeness of the sample.

The existence of another undiagnosed cancer pathology also represents a risk of bias. In the event that this pathology is detected during the follow-up, a statistical analysis will be performed to evaluate the impact of the inclusion of these patients on the results obtained.

### 2.11. Trial status

The PROGLIO trial is currently recruiting. Participant recruitment began in February 2022 and recruitment is expected to finish in August 2023. The approved protocol is version 2, 20/10/2021.

## 3. Discussion

The investigation of blood biomarkers for high-grade glial tumors remains a major challenge in order to predict and monitor treatment response. Identify an accurate circulating biomarker is a highly rewarding area of interest in neuro-oncology. Differents methods have been examined (circulating tumor cells, cell-free DNA, microRNA, exosomes, and proteins) but no single biomarker test seemingly optimal at this time (19). This study, still at the proof-of-concept stage, could confirm that hPG_80_ is measurable in patients with high-grade glial tumors. If the main hypothesis of the PROGLIO trial is confirmed, further research will be required to demonstrate the clinical value of this blood biomarker. A study with a larger, multicentric enrolment would then enable its prognostic and diagnostic roles to be assessed, and to potentially highlight the usefulness of hPG_80_ as a blood biomarker.

## Ethics statement

The studies involving human participants were reviewed and approved by French Ethics Committee (Comité de protection des personnes Ouest III). The patients/participants provided their written informed consent to participate in this study.
